**OFFICIAL USE ONLY**

NUS-IRB Application Form (for HBR)

(IRB-FORM-H02)

|                                        |                                                                                                                                                                                                                                                                                        |           |
|----------------------------------------|----------------------------------------------------------------------------------------------------------------------------------------------------------------------------------------------------------------------------------------------------------------------------------------|-----------|
| Visit 1 (T 1 )              | 1. Treatment allocation and giving out research materials (smart watch, instructions, downloading of mobile phone application)
2. Personal demographics and related questions
3. NCA
4. Physical frailty measures
5. IPAQ
6. Secondary measures (PSQI, BARSE, GDS, GAI) | 2 hours   |
| Visit 2
(T 2 = 3 months) | 1. NCA
2. Physical frailty measures
3. IPAQ
4. Secondary measures (PSQI, BARSE, GDS, GAI)                                                                                                                                                                                     | 1.5 hours |
| Visit 3
(T 3 = 6 months) | 1. NCA
2. Physical frailty measures
3. IPAQ
4. Secondary measures (PSQI, BARSE, GDS, GAI)
5. Return the smart watches                                                                                                                                                      | 1.5 hours |

(iii) Subjects will be recruited over a period of 4 months.

4.2 *Are you recruiting adults or minors who lack mental capacity, or minors who lack sufficient understanding and intelligence to give consent?* ☐ Yes, please specify: \_\_\_\_\_ ☒ No

*If Yes, please explain why there are reasonable grounds for believing that biomedical research of comparable effectiveness cannot be carried out without the participation of the class of persons to which the adult/minor belongs.*

4.3 *Include details on sample size calculation and the means by which data will be analysed and interpreted.*

Given a hypothesized treatment effect size of 0.4 according to previous similar studies, it was estimated using G\*Power that a total sample size of 42 was required to detect a significant within-between interaction with a power of .80 (assuming  $\alpha = .05$ ; correlation between repeated measures = .50; nonsphericity correction = 1). After considering for potential drop-out rates and publication value, a total sample size of N=60 was reached. Given that our valid sample size (N = 60) is larger than 42, our sample size is more than adequate to detect an effect size of 0.4 or larger, at a power of .80 if such effect exists.

The intervention outcomes will be analysed using repeated measures analysis of variance (ANOVA) and linear mixed models.

4.4 *What are the reasonably foreseeable risks, discomforts or inconveniences to a living research subject arising from this biomedical research and/or removal of tissue? Please also*

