**\*\* IMPORTANT - Please complete ALL sections.**

## **V. ABSTRACT OF RESEARCH PROPOSAL**

***In no more than 300 words***, describe concisely the specific aims, hypotheses, methodology and approach of the application, indicating where appropriate the application's importance to science or medicine. The abstract must be self-contained so that it can serve as a succinct and accurate description of the application when separated from it. Please use lay terms and spell out all acronyms when they are used the first time. If it is not possible to use lay terms, the technical and medical terms should be explained in simple language.

Our study aims to explore the role of technology -- in the form of smart watches and mobile phone application -- in physical activity enhancement on cognitive frailty outcomes. Cognitive frailty is defined here as having both physical frailty and cognitive impairment but does not satisfy criteria for Major Neurocognitive Disorder. We postulate that for pre-frail older adults with mild cognitive impairment, such technology will help increase engagement in physical activity with subsequent improvement in cognitive and physical outcomes at follow up. This is with the aim of preventing this particular group from deteriorating to cognitive frailty because of the accompanying increased risk for adverse outcomes and morbidity.

This pilot study will be a randomized control trial with 2 treatment arms. Assessments will be done prior to and following the intervention period. During the period of intervention, the wearable will act as a tracking device and will be paired with a mobile application to issue prompts to the participant when necessary. The independent variable explored in the study is the use of the wearable while the levels of physical and cognitive improvements are the dependent measures. These will be tracked at baseline, 3 months and 6 months. Additionally, the mediating variable measured is the levels of physical activity to ensure that the proposed outcomes are affected through an increased level of physical activity encouraged by the use of the device.

If innovations like technology and the role of self-management proves efficacious, the future of healthcare in the context of a rapidly aging population will be more sustainable. Furthermore, this supporting role of technology in positive behavioral modification amongst older adults can have a multitude of applications in subsequent healthcare interventions.

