#### OFFICIAL USE ONLY

NUS-IRB Application Form (for HBR)

(IRB-FORM-H02)

activity of the older adults via the number of steps taken and number of hours of moderate physical work (based on heart rate). Heart rate and steps will be tracked whenever participants are wearing the watch, which is when they are awake. The watch is to be charged every night when they are sleeping. Participants will have to log down their physical activity by activating the physical activity tracker either on the watch or on the mobile application. If they did not hit the required level of physical activity, they will be sent a notification prompt through the mobile application with details of nearby workout locations as recommendation. For the control group, they will wear the wearables as a tracking device. No prompts will be given and the mobile application will only be installed but not used for this group.

The physical activity guidelines for participants will be 150 minutes of moderate intensity exercise in a week and 7500 steps daily. The technology's capability was developed in collaboration with students from Ngee Ann Polytechnic's School of Engineering. The wearable smart watch used will be the Fossil Smartwatch Sloan HR which enables tracking of the participant's heart rate and steps taken. Those in the intervention group will be able to view this information. However, the control group will not be able to obtain these information and their smart watches will be modified to only show them the time. The mobile application will be linked to the smart watches that participants wear. Participants have to own an Android phone which can support at least a version 6.0 Operating System. The application is meant to be a form of tracking and encouragement of physical activity for those in the intervention group. It will provide reminders in the form of push notifications if participants fail to reach their target for levels of physical activity. Two prompts – once at mid-day and once in the evening – will be sent out if target steps are not reached. Another prompt will be sent out in the middle of the week if target moderate intensity exercises are not reached. Those in the control group will not be receiving the reminders and notifications from the mobile application.

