Baseline information on their personal demographics, neurocognitive data, physical activity and physical frailty will be collected. Level of physical activity is measured using objective data from the smart watch and the International Physical Activity Questionnaire (IPAQ) which collects information on hours of vigorous and moderate physical activity, walking and sitting by the participant in the last 7 days. The FRAIL questionnaire, a simple screening test for frailty in many elderly community samples, hand grip strength, Gait speed, Timed Up and Go (TUG) and a portion of the Short Physical Performance Battery (SPPB) will be used to measure physical frailty. A test battery of NCA that was used in the CHI study will be administered. This includes various commonly used measures of cognition: Rey Auditory Verbal Learning Test (RAVLT), Digit Span Forward and Backward (DS), Colour Trails Test (CTT), Wechsler's Block Design (WBS) and Semantic Verbal Fluency – Animals (SFA). In the event that social distancing measures due to COVID-19 are still in place, the Cambridge Neuropsychological Test Automated Battery (CANTAB) will be used to assess cognitive outcome instead. It is a computerized cognitive test, useful for tracking cognitive changes over time.

Follow up assessments of both cognitive and physical outcomes will be done at 3 months and 6 months. Follow up assessments allow us to test the sustainability of this intervention and to rule out novelty effects. Secondary variables such as sleep quality, levels of motivation, anxiety and depression will be included in the data collection. The questionnaires used are Pittsburgh Sleep Quality Index (PSQI), Barriers Self-Efficacy Scale (BARSE), Geriatric Depression Scale (GDS) and Geriatric Anxiety Inventory (GAI).

(ii) In all, participants will have to make 3 research visits and their entire participation will last 6 months.

|  |            |          |
|--|------------|----------|
|  | Procedures | Duration |
|--|------------|----------|

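### The Visit 1 schedule lists allocation and hand-out of the arm-specific watch ahead of the baseline tests, so those tests can be taken with the arm already known

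*Protocol*

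**What the plan says.** The table in section 4.1(ii) numbers the procedures at each visit. Visit 1 (T1, 2 hours) opens with "Treatment allocation and giving out research materials (smart watch, instructions, downloading of mobile phone application") and continues with "2. Personal demographics and related questions 3. NCA 4. Physical frailty measures 5. IPAQ 6. Secondary measures (PSQI, BARSE, GDS, GAI"). Visit 3 ends with "5. Return the smart watches", after all the tests. The text above the table states that "participants will have to make 3 research visits and their entire participation will last 6 months", so T1 is the only baseline occasion.

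Section 4.1(i) describes how the devices differ. For the intervention arm, heart rate and steps are on display: "Those in the intervention group will be able to view this information". For the control arm, "their smart watches will be modified to only show them the time". Both arms receive a watch and have the app installed, but only the intervention arm uses the app and gets prompts.

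On timing, the abstract (section V) says "Assessments will be done prior to and following the intervention period". Section 7.2 puts consent before any study procedure. Section 4.3 powers a within-between interaction and names repeated measures ANOVA and linear mixed models as the analyses.

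**The concern.** A baseline is most useful when it cannot be influenced by the assigned arm. If the schedule is followed in the order listed, the participant already holds an activity-tracking watch or a time-only watch, with instructions, when the T1 measures are taken.

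Many of those measures can respond to that knowledge. FRAIL, IPAQ, PSQI, BARSE, GDS and GAI are self-reported. Grip strength, gait speed, TUG, the SPPB items and the cognitive tests depend on effort and, in part, on the person administering them. BARSE, used as the motivation measure, is an obvious candidate.

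The planned test compares change over time between arms, with T1 as its starting point. A distortion at T1 that differs by arm and is absent or different later becomes part of the estimated effect. It cannot be separated from a treatment effect once the data are in.

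**Working it through.** **Order of procedures.** No sentence says that the numbered items form a fixed sequence, so the order has to be inferred:

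- Allocation and hand-out carry number 1 at Visit 1, and the T1 measures carry numbers 2 to 6.
- Watch return is last at Visit 3, where it belongs in time. This supports reading the numbers chronologically.
- There are three visits in all, at baseline, 3 months and 6 months, so no earlier visit can hold the baseline.
- The telephone questions in section 8.1 come before consent, but they screen for eligibility and are not the T1 measures.
- No other text puts T1 testing before allocation.

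**The plan's own figure.** Section 4.3 gives a total of 42 for effect size 0.4, power .80, α = .05, correlation .50 and nonsphericity correction 1. The noncentral F calculation for a within-between interaction, with k groups and m time points, uses λ = f²·N·m/(1 − ρ), df1 = (k − 1)(m − 1) and df2 = (N − k)(m − 1).

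- With k = 2, m = 3 and f = 0.2 (0.4 read as a standardised difference d, f = d/2): λ = 0.04 × 42 × 3 / 0.5 = 10.08, df = 2 and 80, power .803. N = 42 is reproduced.
- With f = 0.4 the required N would be 12 (m = 3) or 16 (m = 2). With f = 0.2 and m = 2 it would be 52.
- At N = 60 with f = 0.2 and m = 3, power is .929.

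The planned numbers are therefore consistent with d = 0.4 and three time points including T1. None of them depends on the order of procedures at Visit 1.

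**How a shift enters the estimate.** Let b0 be the between-arm shift caused by knowledge of arm at T1, and b1 the shift at follow-up, both in SD units.

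- Bias of the change-from-baseline contrast = b1 − b0. If the shift persists equally (b1 = b0) it cancels. If it occurs only at T1 (b1 = 0), the bias is −b0.
- With T1 as a covariate and slope .5, a T1-only shift gives a bias of −0.5·b0.

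**Illustration.** These assumptions are not in the protocol: 30 per arm (N = 60 split equally), one follow-up, correlation .5, unit SD, no true effect, T1-only shift, normal approximation. With weight w on the baseline difference (w = 1 for change, w = .5 for the covariate version):

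SE = √[(1 + w² − 2w × .5) × 2/30]

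This is √(1 × 2/30) = 0.258 for w = 1 and √(0.75 × 2/30) = 0.224 for w = .5. Two-sided type I error is Φ(−1.96 − w·b0/SE) + 1 − Φ(1.96 − w·b0/SE).

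| T1-only shift b0 (SD) | Change contrast | T1 as covariate |
|---|---|---|
| 0 | .050 | .050 |
| 0.1 | .067 | .056 |
| 0.2 | .121 | .073 |
| 0.3 | .213 | .103 |

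For b0 = 0.1 and w = 1, b0/SE = 0.1/0.258 = 0.387, which gives .067. Against a standardised difference of 0.4, shifts of 0.1 and 0.3 SD are 0.1/0.4 = one quarter and 0.3/0.4 = three quarters of the hypothesised effect.

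**The case against.** The strongest reply is that the table column is headed only as procedures, that watch return at Visit 3 is a single cue to chronology, and that staff may in practice test first. That is fair as to what will happen on the day. It does not help the document: the listed order is the only one given, and staff who follow it will allocate first.

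Other replies limit how far the point goes, and they stand:

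- A reader might infer that the schedule contradicts the abstract. It does not. The abstract places assessments before the intervention period and does not mention allocation. Tests done in the same visit as hand-out can still precede months of prompts and tracking.
- A reader might infer that all baseline data are compromised. Demographics are essentially fixed. IPAQ covers the previous 7 days, so only its reporting can shift. CANTAB, the COVID-19 alternative, is computerised, which limits rater influence.
- A reader might infer that the person who sets up the watch also runs the tests. The protocol does not say who allocates, configures or assesses. All that follows is that staff present at hand-out can know the arm.
- The arm can also be known at 3 and 6 months, so a persistent reporting shift would partly or wholly cancel. The direction is open too. Where higher scores are better, extra effort in the intervention arm at T1 would hide an effect, while extra effort in the control arm would exaggerate one.
- Participants might withdraw on learning their arm before any T1 value exists. This is possible but speculative, and the cohort diagnosis and screening answers would still describe them in part.
- The trial is a pilot, and no stated figure changes.

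**Conclusion.** The point holds as a matter of procedure order. As written, allocation and hand-out of a visibly arm-specific watch come before the T1 cognitive, frailty, IPAQ and questionnaire measures. This exposes the reference point of the group-by-time interaction to knowledge of arm, and it can be avoided. The conclusion rests on reading the numbered list as a sequence, which the document supports but does not state outright.

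The bias is a risk, not an established amount. It arises only from a shift that differs by arm and does not persist equally at follow-up, and the document gives neither its size nor its direction. The type I error range of about .07 to .21 for T1-only shifts of 0.1 to 0.3 SD belongs to the stated assumptions. With T1 as a covariate the range is about .06 to .10, but section 4.3 does not specify that adjustment. It would be wrong to read these figures as the error rate the trial will have.

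**What to change.** Move item 1 to the end of the Visit 1 list. Consent (already first under section 7.2), demographics, NCA, physical frailty measures, IPAQ and secondary questionnaires are then completed before allocation is revealed, and only afterwards are the watch and app configured and handed out. Say in section 4.1(ii) that the items are done in the order listed. Reword the sentence in the abstract to state that baseline assessments precede allocation.

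This costs an edit to the table, the abstract and any visit checklist. The same staff and the same 2 hours suffice, and N = 42 and N = 60 are unaffected.

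Reordering does not solve one item. Section 4.1(i) counts watch data as part of the measurement of physical activity, and these can be collected only once the watch is worn. State that watch data collected after hand-out are not a pre-allocation baseline. If a pre-allocation watch value is wanted, it would need a separate period of wear before allocation with the same display and no prompts for everyone, which is a larger change and not cost-free.

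### Section 4.3 does not say what kind of effect size 0.4 is; N=42 reproduces only through a conversion that does not suit the interaction test, so 80% power for 0.4 is not supported

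*Protocol*

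**What the plan says.** Section 4.3 of the protocol starts from the phrase "Given a hypothesized treatment effect size of 0.4 according to previous similar studies". It reports, from G*Power, that "a total sample size of 42 was required to detect a significant within-between interaction with a power of .80", with alpha .05 and "correlation between repeated measures = .50; nonsphericity correction = 1". It then raises the total to 60, citing possible drop-out and publication value without giving a drop-out rate, and concludes: "Given that our valid sample size (N = 60) is larger than 42, our sample size is more than adequate" to detect 0.4 or larger at 80% power. The planned analyses are repeated-measures ANOVA and linear mixed models.

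Two inputs that G*Power needs are missing from section 4.3 but appear in the abstract (section V): "This pilot study will be a randomized control trial with 2 treatment arms", and, of the outcomes, "These will be tracked at baseline, 3 months and 6 months". Nowhere does the protocol say whether 0.4 is Cohen's f or Cohen's d.

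**The concern.** In the software's default setting, the within-between interaction routine takes Cohen's f, defined on the interaction itself. Behavioural intervention studies more often report a standardised mean difference, d. The two scales differ by a factor of two even in the simplest two-group comparison, and by more for an interaction. If a d was turned into f with the simple two-group rule, the power statement describes a much larger effect than the text names.

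At stake is the explicit assurance that the trial can detect 0.4 with 80% power. If that assurance is wrong, a non-significant interaction could be read as evidence that the watch and prompts do not work, when the test would have missed a true 0.4 SD difference at least two times in three.

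**Working it through.** **Inputs.** Section 4.3: effect size 0.4, alpha .05, power .80, correlation rho = .50, nonsphericity correction 1, within-between interaction. Section V: k = 2 arms, m = 3 visits. Equal allocation is assumed, because no ratio is stated.

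**Formula.** Noncentral F as in G*Power's default option: lambda = f² × N × m / (1 − rho), df1 = (k − 1)(m − 1) = 2, df2 = (N − k)(m − 1) = 2(N − 2).

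**Step 1: reproduce 42.**

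- f = 0.4, N = 12: lambda = 0.16 × 12 × 3 / 0.5 = 11.52, df 2 and 20, power .810. So f = 0.4 needs 12. At N = 42 its power exceeds 99.9%.
- f = 0.2, N = 42: lambda = 0.04 × 42 × 3 / 0.5 = 10.08, df 2 and 80, power .803. N = 40 gives .782. So f = 0.2 needs exactly 42. At N = 60 its power is .929.
- Other settings tried with 0.4, rounded up to equal arms: the two alternative effect-size options give 34 and 32 (three visits) or 54 and 52 (two visits); the between-factor test gives 36 or 40. None gives 42.

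The figure therefore reproduces if 0.4 is a d and was entered as f = d/2 = 0.2.

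**Step 2: what f is for the interaction.** Let d_t be the difference between arms at visit t in outcome-SD units, and d̄ its mean over the three visits. The interaction effect is f² = mean over visits of [(d_t − d̄)/2]².

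- Constant difference d/d/d: every deviation is 0, so the interaction f is 0. The whole difference is a group main effect, whose f is d/2. This is the case in which halving is right.
- Step, 0/d/d: d̄ = 2d/3, half-deviations −d/3, d/6, d/6, so f² = (d²/9 + d²/36 + d²/36)/3 = d²/18.
- Linear, 0/(d/2)/d: d̄ = d/2, half-deviations −d/4, 0, d/4, so f² = (d²/16 + d²/16)/3 = d²/24.

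Randomisation makes the arms equal at baseline in expectation, so the step and linear patterns are the relevant ones. For f = 0.2 the follow-up difference is 0.2 × √18 = 0.85 SD (step) or 0.2 × √24 = 0.98 SD (linear).

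**Step 3: power for a true follow-up difference of 0.4 SD.**

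| Pattern | Interaction f | lambda at N=42 | Power at N=42 | lambda at N=60 | Power at N=60 |
|---|---|---|---|---|---|
| Step 0/0.4/0.4 | 0.4/√18 = 0.094 | 2.24 | 24% | 3.20 | 33% |
| Linear 0/0.2/0.4 | 0.4/√24 = 0.082 | 1.68 | 19% | 2.40 | 26% |

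**Step 4: difference detectable at 80% power, 2-df interaction.**

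| Analysed | Smallest f | Step | Linear |
|---|---|---|---|
| 42 | 0.199 | 0.85 SD | 0.98 SD |
| 60 | 0.166 | 0.70 SD | 0.81 SD |

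**Step 5: the 60.** The total of 60 was set after allowing for drop-out, so it is an enrolment figure. Comparing it with the required 42 as if all 60 were analysed uses the allowance as surplus power. The difference is 60 − 42 = 18 participants. How many of those are expected to be lost cannot be derived, because no rate is given and publication value was also a reason for the increase.

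**The case against.** The best defence is that 42 is not a miscalculation. With 0.4 taken as d, f = 0.2, two arms and three visits, the software returns exactly 42. That stands. A reader might infer that 42 simply does not follow from the inputs; the document does not support so flat a claim, because it leaves the metric open and one natural reading gives 42. The fault is the undeclared metric and the conversion.

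The low power figures are also conditional. They need 0.4 to be a follow-up difference in SD units, and the earlier studies it was taken from cannot be checked here. If 0.4 really is an interaction f, power at 42 is close to 100%; but then 42 is far more than the 12 required and remains unexplained. They also belong to the omnibus interaction test alone. For the step pattern with 60 analysed, a single contrast of mean follow-up minus baseline has about 43% power, and a baseline-adjusted comparison of mean follow-up about 59% (normal approximation). So 24% to 33% is not the power of every analysis the plan could lead to, though all of these remain below 80%.

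A reader might also divide 42 by 60 and infer a planned 30% drop-out. The protocol states no such rate, and drop-out was not the only reason for 60.

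Lastly, the study calls itself a pilot and a feasibility study, for which low power is acceptable. That is a good reason not to ask for more participants. It does not excuse an explicit statement of adequacy that the design does not bear out.

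**Conclusion.** The point holds in this form: section 4.3 leaves the metric of 0.4 undefined, and on the reading that yields 42 the power claim is wrong for the test named. A true follow-up difference of 0.4 SD would be detected by the interaction test with a probability of about 19% to 33%, depending on the time pattern and on whether 42 or 60 are analysed. This rests on equal allocation, equal arms at baseline, the protocol's own correlation of .50 and sphericity, and 0.4 being a standardised mean difference. The last is an inference from the match at 42, not something the protocol states. On the other reading, f = 0.4, the required number is 12 and the stated 42 is unexplained. Either way the paragraph cannot stand as written. Separately, the comparison of 60 with 42 treats enrolled participants as analysed ones.

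**What to change.** Keep N=60 and rewrite section 4.3:

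- Say whether 0.4 is Cohen's f or d, and give the number of arms, the number of visits and the assumed time pattern with the other inputs.
- Replace the statement that the sample is more than adequate for 0.4 with the difference detectable at 80% power by the 2-df interaction: about 0.70 SD (step) or 0.81 SD (linear) with 60 analysed, and about 0.85 SD or 0.98 SD with 42 analysed.
- State the drop-out rate that the sponsor itself assumes, and base the power sentence on the expected number of completers. A rate of 30% should not be adopted merely because 42/60 = 0.70.
- Stop calling 60 the valid sample size; it is the enrolment target.

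The cost is one paragraph and a less favourable stated detectable effect. No participants, visits or procedures change.

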## **6. Characteristics of Target Research Subjects (Prospective Recruitment Only):**

6.1 *What is the number of research subjects to be enrolled? Give a breakdown by site of recruitment for multi-centred studies.*

| Site(s) of Recruitment                                            | Total | Adults (at least 21 years old) | Minors (below 21 years old and never married) |
|-------------------------------------------------------------------|-------|--------------------------------|-----------------------------------------------|
| National University of Singapore (Mind Science Center, CHI Study) | 100   | 100                            | 0                                             |

6.2 *Lower Age Limit:* 60

*Upper Age Limit:* 85

Total number of research subjects targeted for enrolment worldwide (for international multi-centred studies): Not Applicable

6.3 *Are there any recruitment restrictions based on race or gender of the participant? If yes, please elaborate. If no, please state "Not Applicable".*

Not Applicable

6.4 *Inclusion criteria:*

1. Older adults aged 60 to 85 years
2. Has Mild Cognitive Impairment based on their cognitive diagnosis in the CHI study. These participants were previously diagnosed based on a consensus from a panel of psychiatrists/psychologists who reviewed the Mini-Mental State Examination (MMSE), a Neurocognitive Assessment (NCA) test battery and Clinical Dementia Rating (CDR) scores.
3. Pre-frail as determined by having a score of 1 or 2 on the FRAIL Questionnaire

6.5 *Exclusion criteria:*

1. Engages in vigorous exercises as determined by having more than 0 minutes of vigorous exercise on the International Physical Activity Questionnaire (IPAQ).
2. Has medical contraindications for exercising, including but not limited to: physical disabilities or heart conditions where the primary doctor disallows exercising at moderate intensity.
3. Does not own an Android phone which can support at least a version 6.0 Operating System

6.6 *Are the research subjects vulnerable or in a dependent relationship with the researchers? (e.g. teacher-student relationship, supervisor-staff relationship)*

☐ Yes

☒ No

☐ Not applicable

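### Neither of the two named analyses is designated as deciding, and the powered interaction uses baseline as an outcome; one baseline-adjusted mixed model with a pre-set contrast would use the data better

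*Protocol*

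**What the plan says.** Protocol section 4.3 gives the whole analysis in one sentence: "The intervention outcomes will be analysed using repeated measures analysis of variance (ANOVA) and linear mixed models". Both methods apply to the same outcomes, and neither is called primary.

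The sample-size paragraph just above it starts from an effect size: "Given a hypothesized treatment effect size of 0.4 according to previous similar studies". The metric of 0.4 is not named. The target is "to detect a significant within-between interaction with a power of .80", with "correlation between repeated measures = .50; nonsphericity correction = 1", and the result is that "a total sample size of 42 was required". The planned number follows: "After considering for potential drop-out rates and publication value, a total sample size of N=60 was reached". No drop-out rate is given.

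The abstract and the visit table in section 4.1 place assessments at baseline, 3 months and 6 months. Section 4.1 also says that the follow-ups serve to test sustainability and to rule out a novelty effect.

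**The concern.** Two features of this wording work against the trial.

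- **No deciding analysis.** With missing visits the two methods use different participants. Standard repeated-measures ANOVA needs all three measurements, whereas a likelihood-based mixed model keeps partial follow-up. They can give different answers, and nothing says which one counts. The question recurs for each cognitive and physical outcome.
- **Baseline as an outcome.** A group-by-time interaction over three visits compares changes from baseline. It subtracts the whole baseline value instead of adjusting for it with the weight that the correlation supports. In a randomised trial this discards precision that the baseline, collected anyway, could supply.

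At stake are a choice of result after the data are seen, and avoidable loss of power in a small study.

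**Working it through.** **Inputs.** From section 4.3: effect 0.4, alpha 0.05, correlation rho = 0.5, sphericity correction 1, N = 42 and N = 60. From the abstract and section 4.1: two arms and three assessments (m = 3). Assumed, because not stated: 1:1 allocation, two-sided t tests and, for steps 2 to 4, full retention.

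**1. Reproduce the protocol's figure.** For the interaction, lambda = N·m·f²/(1 − rho), with df = (m − 1) and (N − 2)(m − 1).

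- f = 0.2, m = 3, N = 42: lambda = 42 × 3 × 0.04/0.5 = 10.08, df 2 and 80, power 80.3%. This matches.
- With m = 2 and f = 0.2, N would be 52. With m = 3 and f = 0.4, N would be 12.
- At N = 60 the matching inputs give lambda = 14.4 and power 92.9%.

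So 42 corresponds to f = 0.2 (half of 0.4) and three measurements. The only three assessments include baseline, so the powered test is the 2-df interaction with baseline among the outcomes.

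**2. The same test if 0.4 is a between-arm difference in SD units at both follow-ups.** Arm differences are (0, 0.4, 0.4), with mean 0.267. The squared deviations sum to 0.0711 + 0.0178 + 0.0178 = 0.1067. Then lambda = (60/4) × 0.1067/0.5 = 3.2 and power is 33.3%. This pattern has f = 0.4/√18 = 0.094. Reaching f = 0.2 would take 0.2 × √18 = 0.85 SD at both follow-ups.

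**3. Effect of baseline adjustment, like for like** (N = 60, rho = 0.5). SE = √(2 × variance/30), and the noncentrality of the 1-df contrasts is 0.4/SE. Variances are in units of σ².

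- Average of months 3 and 6. Change from baseline: (1 + rho)/2 + 1 − 2rho = 0.75. Adjusted: (1 + rho)/2 − rho² = 0.50.
- Month 6 alone. Change: 2(1 − rho) = 1.00. Adjusted: 1 − rho² = 0.75.
- Joint 2-df test. The unadjusted form is step 2. Given baseline, each follow-up has variance 0.75 and their covariance is 0.25, so lambda = 15 × 2 × 0.16/(0.75 + 0.25) = 4.8.

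| Test | Change from baseline | Baseline-adjusted |
|---|---|---|
| Average of months 3 and 6, 1 df | noncentrality 1.79, 42.1% | 2.19, 57.7% |
| Month 6 alone, 1 df | 1.55, 33.2% | 1.79, 42.0% |
| Joint, 2 df | lambda 3.2, 33.3% | 4.8, about 46% |

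A simulation of 20,000 trials gave 32.3% for the interaction and 56.2% for the adjusted average.

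**4. Sensitivity at N = 60, difference 0.4 at both follow-ups.**

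| rho | 2-df interaction | Average: change → adjusted | Month 6: change → adjusted |
|---|---|---|---|
| 0.3 | 24.7% | 31.8% → 53.0% | 25.1% → 35.8% |
| 0.5 | 33.3% | 42.1% → 57.7% | 33.2% → 42.0% |
| 0.7 | 52.0% | 62.2% → 71.8% | 50.3% → 56.9% |
| 0.8 | 70.6% | 79.4% → 84.8% | 67.3% → 71.8% |

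- With 48 completers (20% loss, assumed) and rho = 0.5, the interaction has 27.1%, and the average goes from 34.7% to 48.3%.
- With a gradual effect (0, 0.2, 0.4) and rho = 0.5, the interaction has 25.8% and the adjusted average 36.5%. Month 6 alone, adjusted, stays at 42.0%.
- For 80% power at (0, 0.4, 0.4) and rho = 0.5, N = 184 is needed for the interaction and N = 102 for the adjusted average.

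**The case against.** The best defence is that this is a short ethics form for a pilot. Covariance structure, analysis set and choice of contrast normally belong in a statistical analysis plan, which may exist. Naming two methods leaves a choice open and is not a contradiction. The term linear mixed models already permits a baseline-adjusted model. An averaged contrast also answers a different question from the interaction and cannot by itself show whether an effect lasts.

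Much of this stands, and it rules out several stronger readings that a reader might infer:

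- **That the two methods conflict.** They do not. What is missing is a statement of which one decides.
- **That the mixed model treats baseline as an outcome.** The protocol does not say so. That reading is supported only for the powered interaction.
- **That drop-out from 60 to 42 is planned.** 42 is the calculated requirement. The margin up to 60 is attributed to drop-out and publication value together, with no rate.
- **That the interaction wastes a degree of freedom on something randomisation excludes.** With equal expected baselines, its two degrees of freedom correspond to the month 3 and month 6 differences, and both are possible effects. The loss lies only in how baseline is used.
- **That baseline adjustment alone lifts power from 33% to 58%.** That step also replaces a 2-df test with a 1-df average.

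What the defence does not remove is that section 4.3 commits the outcomes to an analysis that discards incomplete participants, and sizes the trial on a test that uses baseline inefficiently. Those are choices the protocol makes, not details it leaves open.

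**Conclusion.** The point holds as an improvement worth making. The protocol names two analyses with none deciding, and its powered test has baseline as a repeated outcome. At N = 60 and rho = 0.5, baseline adjustment adds about 16 percentage points of power for the average, 9 for month 6 alone and about 13 for the joint test. For both single contrasts a gain appears at every correlation tried, and it shrinks as the correlation rises.

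All of this rests on reading 0.4 as a between-arm SD difference present at both follow-ups, with equal arms and full retention. It would be wrong to report 33% as the trial's stated power: on the protocol's own inputs the figure at 60 is about 93%. That gap comes from the metric of 0.4, which is a separate sample-size question. On the SD reading, the adjusted average still has only 58% at N = 60 and rho = 0.5, so the change makes better use of the data without rescuing the sample size.

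**What to change.** In section 4.3, make one linear mixed model the deciding analysis:

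- Responses: months 3 and 6.
- Fixed effects: baseline value, arm, visit, arm-by-visit and baseline-by-visit.
- Participants: all randomised with at least one follow-up, analysed as allocated.
- One contrast fixed in advance, either the average of months 3 and 6 or month 6 alone. The average is stronger if the effect is similar at both visits; month 6 is stronger if the effect builds up gradually.
- Month 3 and month 6 effects also reported separately with 95% confidence intervals, so that sustainability can be judged.
- Repeated-measures ANOVA dropped, or kept as a labelled sensitivity analysis.

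Restate the sample-size paragraph for the chosen contrast, naming the metric of 0.4 and the assumed retention. State which N applies as well, since the enrolment table in section 6.1 reads "National University of Singapore (Mind Science Center, CHI Study) | 100" against 60 in section 4.3.

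The cost is a rewrite of two short paragraphs and the commitment to one contrast before the data are seen. Baseline is already measured at Visit 1, so no visits or assessments are added.
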